### Sample size, power, and statistics

#### Feasibility analysis

As this is a feasibility study, it is not designed or powered to evaluate statistically significant changes in any of the parameters being assessed. Therefore, a qualitative synthesis of feasibility data will be reported.

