### Primary outcome measures

The primary outcomes for this study are (1) the feasibility and (2) safety of FMT as an adjunctive treatment for MDD in adults. The study outcomes, participant appointment schedule, and study timeline are outlined in Table 1 and Fig. 1.

Feasibility will be considered as a composite outcome, measured by the following:The ability to meet recruitment targets (measured by recruitment logs, comparing actual recruitment against projected targets)Participant retention and completion rates (measured by attrition rates and completeness of data)Adherence to intended protocol (measured by completion of intervention as planned, missed appointments, technical difficulties arising, and completeness of study data)Participant acceptability (measured using the TransCelerate Study Participant Feedback Questionnaire, plus the addition of questions designed specifically for this study)Robustness of study methodology, including effectiveness of blinding (measured qualitatively based on feedback from researchers throughout and at the conclusion of the study, and a participant and researcher survey to assess blinding)

Safety of FMT as an adjunctive treatment in adults will be measured by an assessment of adverse events. These data will be collected through direct observations by the study nurse during administration of the intervention, and via participant reporting during the intervention and each appointment thereafter (measured at weeks 0, 2, 4, 6, 8, and 26). Participants will also be encouraged to contact the research team at any time to report adverse events outside of study appointments.

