
### Feasibility targets

Table 4 outlines pre-specified targets identified by the research team as a minimum standard that would indicate that the study design was feasible. These targets will also assist the study team to identify aspects of the trial that may need to be amended to improve future, large-scale trials.

**Table 4 Tab4:** Feasibility targets

Target area	Feasibility target
Recruitment	Successful enrolment of *n* = 15 participants across a 6-month active recruitment period
Retention	A minimum of *n* = 10 participants to complete study until the 8-week primary endpoint (i.e. a 33% attrition rate).
Adherence to protocol	Participants should: 1) Receive two of the total four enemas 2) Attend their baseline, week 2 and week 8 appointments 3) Provide baseline and week 2 stool samples
Safety	Nil severe and/or serious adverse events rated as likely due to study intervention in the active FMT group.
Adequacy of blinding	The best achievable outcome for adequacy blinding is participants and researchers correctly guessing allocation at a rate of 50% (the rate due to chance). Whilst we are not likely to be statistically powered to measure this outcome, we aim to reach an outcome approaching 50%.

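### The only analysis named for the feasibility data is a qualitative synthesis, justified by lack of power, although several components are rates or counts; 10 of 15 retained is compatible with attrition of about 12% to 62%

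*Protocol article*

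**What the plan says.** Under Primary outcome measures, the protocol article treats feasibility as a composite and defines parts of it numerically. Recruitment is compared with projected targets, and retention is listed as "Participant retention and completion rates (measured by attrition rates and completeness of data").

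Under Feasibility targets, Table 4 is introduced as "pre-specified targets identified by the research team as a minimum standard that would indicate that the study design was feasible". Its recruitment row reads "Successful enrolment of *n* = 15 participants across a 6-month active recruitment period", and its retention row "A minimum of *n* = 10 participants to complete study until the 8-week primary endpoint (i.e. a 33% attrition rate"). The adherence row lists what each participant should do (enemas received, visits attended, stool samples given) but not what share of participants must do it. The blinding row aims for a correct-guess rate close to 50%.

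The Feasibility analysis section then says of the study that "it is not designed or powered to evaluate statistically significant changes in any of the parameters being assessed", and draws the conclusion "Therefore, a qualitative synthesis of feasibility data will be reported". No other analysis of the feasibility data is described. The Gut microbiota analyses section, by contrast, names specific tests and a multiplicity correction for the secondary outcome.

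**The concern.** The stated reason does not support the stated method. Low power means that a hypothesis test would be uninformative. It does not stop anyone from estimating a proportion and showing how well it is known, and a small sample makes that display more necessary. The method also fits the data poorly: an attrition rate, a correct-guess rate and a share of adherent participants are quantities.

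The practical stake is the next trial. The Abstract, the section on data sharing and follow-up research, and the Discussion all make a favourable feasibility result the step to a fully powered trial, and the Discussion says that the pilot results will support and inform it. If retention is described only in words, or set against its target without any measure of precision, planners cannot tell a well-supported rate from one that 15 participants barely pin down.

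**Working it through.** **Inputs.** Planned N = 15 and at least 10 completers at week 8 (Table 4). The article states no confidence level, so a two-sided 95% level is assumed.

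**The plan's own figure.** Attrition at the retention target = (15 − 10)/15 = 5/15 = 33.3%. This reproduces the 33% in Table 4.

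**Precision at that result.** The exact (Clopper-Pearson) 95% interval for x events in n is:

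- lower limit = 2.5% quantile of Beta(x, n − x + 1)
- upper limit = 97.5% quantile of Beta(x + 1, n − x)

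With x = 5 dropouts and n = 15, these are quantiles of Beta(5, 11) and Beta(6, 10). The result is 11.8% to 61.6% for attrition, which is 38.4% to 88.2% for retention.

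**Sensitivity to the method.** Interval for 5/15:

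| Method | Lower | Upper |
|---|---|---|
| Exact, 95% | 11.8% | 61.6% |
| Wilson, 95% | 15.2% | 58.3% |
| Jeffreys, 95% | 14.0% | 58.4% |
| Agresti-Coull, 95% | 15.0% | 58.5% |
| Wald, 95% | 9.5% | 57.2% |
| Exact, 90% | 14.2% | 57.7% |

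The 62% is the top of this range. Every method leaves attrition well above one half compatible with a result that meets the retention target.

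**Other possible results, exact 95%.**

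| Result | Estimate | Interval |
|---|---|---|
| 12 of 15 retained | 80% | 52% to 96% |
| 15 of 15 retained | 100% | 78% to 100% |
| 8 of 15 correct guesses | 53% | 27% to 79% |

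Even full retention leaves attrition of up to 22% compatible with the data, and a guess rate close to 50% is also compatible with rates far from it. The interval therefore adds information at every plausible result, not only at the margin.

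**The case against.** The strongest reply is that this rests on silence. The article neither plans nor rules out confidence intervals, it condenses a fuller protocol, and interval methods are often left to an analysis plan. It also commits to the CONSORT extension for pilot and feasibility trials. With N published, any reader could derive an interval from a reported count. This stands against the inference that intervals have been excluded: a reader might take the Feasibility analysis section that way, but it does not say so. The reply does not rescue what the section does say. It names a method and gives a reason for it, and the reason does not lead to the method. An unseen plan could add intervals without repairing that sentence.

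Four further readings go beyond the documents:

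- **That 10 of 15 would by itself be declared feasible.** Retention is one component of a composite, and Table 4 has five target areas. The count meets the retention row only.
- **That every component has a numeric target.** Adherence has participant-level criteria and no target proportion, so an estimate for it has no threshold to stand beside.
- **That the chance of passing is part of this defect.** If true retention were 50%, the 10-of-15 target would be met with probability 15%; at 60%, with probability 40%. These figures follow from the target and N alone and would be the same with intervals reported.
- **That the larger trial will take its attrition allowance from this rate.** The article says only that the pilot will support and inform that trial. The one sample-size use that it names concerns symptoms, well-being and functioning.

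The authors do acknowledge limited power for blinding in Table 4. That, too, is an argument about testing rather than about estimating the guess rate.

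**Conclusion.** The point holds as one of analysis choice and rationale. For a primary outcome with several numeric components, the article names only a qualitative synthesis, on a ground that argues against testing but not against estimation. The size is shown by retention: just meeting its target is compatible with attrition of about 12% to 62% by the exact 95% interval, or with an upper limit of about 57% to 58% by the other standard 95% methods. This assumes all 15 participants are enrolled and a two-sided 95% level, which the article does not state.

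The documents do not show that intervals will be withheld, or that a bare retention pass settles feasibility. The matter is worth correcting because the pilot gates and informs a larger trial and because the correction is nearly free, but no stated target or decision rule is wrong on this account.

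**What to change.** Replace the concluding sentence of the Feasibility analysis section so that it provides the following:

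- Retention to week 8, the share of participants who meet the Table 4 adherence criteria, and the correct-guess rate for blinding are each reported as n/N and % with an exact 95% confidence interval.
- Each is set beside its target where Table 4 gives a numeric one (retention and blinding; adherence has none).
- Recruitment is reported as a count against its target.
- The qualitative synthesis is kept for free-text feedback from participants and researchers.
- The conclusion states the range of retention compatible with the data, for use in planning the larger trial.

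The lack of power can remain as the reason for not testing hypotheses. The targets do not change, and no new data or participants are needed. The cost is a change of wording and a feasibility statement that may read slightly less favourably.

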#### Gut microbiota analyses

Longitudinal analysis of changes in gut microbiome composition will be performed within the RStudio [62] environment. Measures of gut microbiota alpha-diversity (e.g. Shannon Index, Simpson Index, Chao-1, ACE, evenness, Faith’s phylogenetic diversity) [63, 64] and beta-diversity (e.g. Bray-Curtis, Jaccard, Aitchison distance) [65] will be calculated for donors (baseline) and recipients (three timepoints: baseline, 2 weeks, 8 weeks post-intervention). Differences in alpha-diversity between donors and recipients (between groups) will be tested using the Mann-Whitney test and between each time point (within groups) will be compared using Kruskal-Wallis non-parametric test. An appropriate method will be used to correct for multiple comparisons. Permutational multivariate analysis of variance (PERMANOVA) and visualization with principal coordinate analysis (PCoA) will be used to estimate any differences in gut microbiota community structure (beta-diversity) between donors and recipients and in recipients over time. Differential abundance analyses will be conducted to compare the taxonomic composition of gut microbiota between donors and recipients and in recipients over time.

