## Methods

### Objectives

The primary objectives for this study are to evaluate the feasibility and safety of FMT as an adjunctive treatment for MDD in adults. The secondary objective is to evaluate the impact of enema-delivered FMT on gut microbiota compared with a placebo enema in adults with MDD. As this study is not powered to evaluate efficacy, exploratory objectives include any changes observed in depression and anxiety symptoms, sleep, quality of life, level of function, gut symptomatology, blood biomarkers of neurogenesis, gut permeability, inflammation, and cardiometabolic parameters following delivery of FMT via enema compared with a placebo enema in adults with depression.

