### Secondary outcome measures

The secondary outcome measure of this study is changes in gut microbiota composition and functional potential, which will be measured via the following:The degree of change in gut microbiota composition and functional potential in recipients, which will be assessed by observing changes in gut microbiota composition (alpha diversity, beta diversity, differential abundance of species) and functional potential at 2- and 8-weeks post-intervention compared with baseline.The degree of microbial ‘engraftment’: degree to which the changes in gut microbiota composition and functional potential of recipients are concordant with the gut microbiota profiles of the donor stool post-active FMT and compared with placebo enema.Donor vs recipient at baseline (0 weeks)Donor vs recipient at 2 weeks (active FMT compared with placebo group)Donor vs recipient at 8 weeks (active FMT compared with placebo group)

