### Trial allocation, sequence generation, and blinding

Allocation to treatment arms will be randomly assigned in a 2:1 ratio using permutated block randomisation. Unblinded researchers independent to the study team, utilising a simple randomisation method, will develop the randomisation sequence and assign participants to study arms. The unblinded researchers will allocate and package enema kits sequentially, and packaging will be identical to conceal treatment allocation and blinding. The study staff, investigators, trial biostatistician, nurses delivering the enemas, and participants will be blinded to group allocations.

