Choice of enema as a delivery route was based upon numerous factors, including feasibility, resource utilisation, safety, tolerability, patient preference, and efficacy. The most poorly tolerated and highest risk deliveries of FMT are via colonoscopy or nasogastric/nasoduodenal delivery [28]. Nasogastric/nasoduodenal delivery methods carry small but non-zero risks of perforation, aspiration, and vomiting, and are technically more complex to perform. Whilst considered the most efficacious, the colonoscopic route is also complex to perform in a research setting; this process requires a gastroenterologist, is more resource intensive, invasive, and has theoretical risks associated with use of sedation, bowel preparation and a risk of perforation, notwithstanding limitations in translation and dissemination [72]. On the other hand, whilst encapsulated FMT is considered a safe and efficacious route [73, 74], this product is not yet widely available in Australia.

Enema delivery is a widely used route of administration for FMT. It has several advantages including availability, safety, tolerability, and efficacy [72]. Additionally, FMT via enema does not require clinician-specific expertise to administer, is more affordable, and generally considered a more feasible option for delivery [72]. FMT via enema has been demonstrated to be efficacious at restoring gut microbiota following disruption by antibiotics [75]. Moreover, it has been shown to be safe and efficacious in the long term [76], and even in higher risk populations such as children [50]. Therefore, in balancing these many considerations, we have chosen FMT via enema as the route of administration for our current study.

The primary limitation of this study is the small sample size, meaning that the study will not be powered to statistically measure any of the intended secondary outcomes, and for this reason these are considered exploratory outcomes rather than secondary outcomes. However, the primary aim of the program is to explore feasibility, which the study has been designed to evaluate. If found to be feasible, a full-scale RCT is planned which would be adequately powered to evaluate efficacy as a primary outcome and will be powered to evaluate the secondary and exploratory outcomes of this feasibility study.

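### The microbiota analysis section gives no analysis of active versus placebo, the contrast that the secondary objective and the engraftment outcome call for

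*Protocol article*

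**What the plan says.** Three parts of the protocol article bear on this.

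- **Objectives.** The randomised contrast is the question: "The secondary objective is to evaluate the impact of enema-delivered FMT on gut microbiota compared with a placebo enema in adults with MDD".
- **Secondary outcome measures.** The first part is change in composition and "functional potential at 2- and 8-weeks post-intervention compared with baseline", with no arm contrast named. The second part, engraftment, is the degree to which recipients' changes are "concordant with the gut microbiota profiles of the donor stool post-active FMT and compared with placebo enema". The list beneath it includes "Donor vs recipient at 2 weeks (active FMT compared with placebo group", and the same contrast at week 8.
- **Gut microbiota analyses.** For alpha-diversity, one test sets donor samples against recipient samples: "Differences in alpha-diversity between donors and recipients (between groups) will be tested using the Mann-Whitney test". A second test looks only at change over time: "between each time point (within groups) will be compared using Kruskal-Wallis non-parametric test". PERMANOVA with principal coordinate plots, and differential abundance, are each set up for the same two purposes: donors against recipients, and recipients over time. The section does not mention placebo and does not say whether recipients are split by arm.

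On allocation: "Allocation to treatment arms will be randomly assigned in a 2:1 ratio using permutated block randomisation". The planned numbers are 10 active and 5 placebo.

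**The concern.** The objective and the analysis do not match. The analysis section does more than stay silent on detail: it lists the comparisons to be made, and its parenthesis attaches the phrase for a between-group comparison to donors and recipients, not to the randomised arms.

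The placebo arm is there to separate the effect of donor material from anything else that moves the microbiota over eight weeks, such as the enema vehicle, diet or the passage of time. Only a comparison of the arms uses it for that. If the arms are pooled, allocation plays no part in the result. If each arm is tested separately, a reader is left to set one p-value from 10 people beside another from 5, and the larger arm is usually the likelier to reach significance when both change equally. What is at stake is the interpretation of the only secondary outcome, which the Discussion expects to yield information on dosing and frequency.

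**Working it through.** **Step 1: match each stated analysis to the contrast required.** The plan gives no power, alpha or effect size for these tests, so there is no figure to reproduce. The check is a side-by-side reading.

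| Analysis in Gut microbiota analyses | What is compared | Active v placebo? |
|---|---|---|
| Mann-Whitney, alpha-diversity | donors v recipients | no |
| Kruskal-Wallis, alpha-diversity | time points within groups | no |
| PERMANOVA / PCoA, beta-diversity | donors v recipients; recipients over time | no |
| Differential abundance | donors v recipients; recipients over time | no |

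Result: 0 of 4 contrast the arms. The engraftment outcome asks for the contrast at 2 of 2 post-baseline visits.

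**Step 2: what separate within-arm tests can do.** This is an illustration; the protocol does not say that it will test each arm separately. Assumptions: 10 active and 5 placebo; baseline, week 2 and week 8; total SD 1; within-person correlation 0.7; the same true shift in both arms from week 2; Kruskal-Wallis in each arm at two-sided 0.05 with no multiplicity correction; 4,000 trials per row. The true difference between arms is zero throughout.

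| Shared shift (SD) | Active p < 0.05 and placebo p ≥ 0.05 |
|---|---|
| 0 | 0.1% |
| 0.3 | 1% |
| 0.5 | 5% |
| 0.8 | 24% |
| 1.0 | 43% |
| 1.5 | 48% |

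The misleading pattern is rare if the placebo arm hardly moves, and common if both arms move by about 0.8 SD or more. The documents do not say which to expect.

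**Step 3: what the direct comparison can deliver.**

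- Smallest attainable exact two-sided Mann-Whitney p without ties: 2/C(n1+n2, n2). For 10 v 5 this is 2/3003 = 0.0007. With the 10 completers that Table 4 sets as the minimum, it depends on the split: 7 v 3 gives 2/120 = 0.017, 5 v 5 gives 2/252 = 0.008, and 9 v 1 gives 2/10 = 0.20. These are floors set by the most extreme ranking, not power.
- Approximate power at 10 v 5 (normal approximation, assumed two-sided 0.05): 0.31 for a standardised difference of 0.8, 0.45 for 1.0 and 0.78 for 1.5. For 80% power the difference must be (1.960 + 0.842) × √(1/10 + 1/5) = 2.802 × 0.548 = 1.53 SD.
- Half-width of a 95% t-interval in SD units of the change score: at 10 v 5, 2.160 × 0.548 = 1.18; at 7 v 3, 2.306 × √(1/7 + 1/3) = 2.306 × 0.690 = 1.59.

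So the contrast is computable from the planned samples, but imprecise.

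**The case against.** The strongest reply is that the contrast is already specified. The secondary outcome section fixes the measure (concordance with donor stool), the arms and the visits for engraftment, and the objective states the same comparison. Only a named analysis is absent, and an article commonly leaves that to a statistical analysis plan. Part of this stands. A reader might infer that the randomised comparison is never planned, and the documents do not support that. What remains is that the analysis section does list its comparisons and the required one is not among them. A later plan would either repeat the mismatch or depart from the published text.

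Three other readings are tempting and go too far.

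- **That donor comparison means nothing in the placebo arm.** It does have meaning: the similarity of placebo recipients to a donor reference is the control against which engraftment is judged.
- **That the donor Mann-Whitney test is bound to fail for want of donors.** The number of donors is not stated, so no such figure can be fixed.
- **That a false FMT claim is likely.** The high percentages need a shared shift of 0.8 SD or more, separate tests by arm, and no multiplicity correction, although the protocol promises some correction.

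It is also fair to say that the outcome is secondary, that the primary outcomes are feasibility and safety, that no target in Table 4 rests on a microbiota result, and that the protocol disclaims power for every parameter. That limits the severity. It does not justify leaving the arms uncompared, because an imprecise estimate of the right contrast is still the estimate that the objective asks for.

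The Discussion's remark that "for this reason these are considered exploratory outcomes rather than secondary outcomes" is loosely worded. The same paragraph later speaks of secondary and exploratory outcomes as separate sets, so it does not settle the status of the microbiota outcome and adds little here.

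**Conclusion.** The concern holds as a mismatch within the document: the objective and the engraftment outcome call for active versus placebo, and none of the four stated microbiota analyses provides it. This conclusion rests on the text alone and needs no numerical assumption.

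The consequence is that following the analysis section as written gives no estimate of the FMT-versus-placebo difference, and a change common to both arms could be credited to FMT. The chance of that is not determined by the documents. Under the stated simulation assumptions it runs from 0.1% to 48% for shared shifts of 0 to 1.5 SD.

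Severity is moderate. Randomisation, sampling and the primary outcomes are unaffected, and an unseen full analysis plan may already supply the contrast.

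**What to change.** In Gut microbiota analyses, make the between-arm comparison the main secondary analysis:

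1. For every recipient in both arms, compute the change from baseline to week 2 and from baseline to week 8 in alpha-diversity and in mean distance to one common donor reference set.
2. Report the active-minus-placebo difference in each change with a 95% interval, either adjusted for baseline or from a permutation test that follows the allocation scheme.
3. If PERMANOVA and differential abundance are to inform the same question, give them an arm-by-time term, with arm labels permuted across whole participants.
4. State that these estimates are unpowered and are to be read as estimates with their intervals.
5. Keep the donor-versus-recipient and within-arm results as description, and state whether recipients are shown by arm.

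The cost is a few sentences and a little analysis code. The recipient stool samples are already scheduled at baseline, week 2 and week 8, and donor diversity is already to be calculated, so no new data are needed. The price in precision is visible in advance: about ±1.2 SD at 10 versus 5, and about ±1.6 SD if only 7 and 3 complete week 8.

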**Methods and design:**

This protocol describes an 8-week, triple-blind, 2:1 parallel group, randomised controlled pilot trial (*n* = 15), of enema-delivered FMT treatment (*n* = 10) compared with a placebo enema (*n* = 5) in adults with moderate-to-severe MDD. There will be a further 26-week follow-up to monitor longer-term safety. Participants will receive four FMT or placebo enemas over four consecutive days. The primary aims of the study are to evaluate feasibility and safety of FMT as an adjunctive treatment for MDD in adults. Changes in gut microbiota will be assessed as a secondary outcome. Other data will be collected, including changes in depression and anxiety symptoms, and safety parameters.

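### The over-time comparison of alpha-diversity uses Kruskal-Wallis, an independent-samples test, on three samples from the same recipients, so its p-values are too large when a person's samples correlate

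*Protocol article*

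**What the plan says.** In the protocol article, the section on gut microbiota analyses opens by promising a longitudinal analysis: "Longitudinal analysis of changes in gut microbiome composition will be performed within the RStudio" environment. Alpha-diversity is to be calculated for donors at baseline and for "recipients (three timepoints: baseline, 2 weeks, 8 weeks post-intervention"). Mann-Whitney is assigned to donors against recipients, and differences "between each time point (within groups) will be compared using Kruskal-Wallis non-parametric test". An unnamed correction for multiple comparisons follows.

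Table 1 schedules stool samples for each participant at weeks 0, 2 and 8. The outcome that these samples serve is stated under the secondary outcome measures: "The secondary outcome measure of this study is changes in gut microbiota composition and functional potential", with composition and "functional potential at 2- and 8-weeks post-intervention compared with baseline".

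The design is a comparison "of enema-delivered FMT treatment (*n* = 10) compared with a placebo enema (*n* = 5"). The feasibility targets (Table 4) accept "A minimum of *n* = 10 participants to complete study until the 8-week primary endpoint (i.e. a 33% attrition rate"). For stool, they require only the baseline and week 2 samples. The feasibility analysis section and the Discussion both state that the study is not powered for these outcomes.

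**The concern.** Kruskal-Wallis ranks all observations together and judges the differences between time points against the total spread of those ranks. That is right when each time point has different people. Here each recipient supplies all three values, so stable differences between people enter the yardstick although they cancel out of the comparison over time. The test therefore discards the pairing that repeated sampling provides.

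Kruskal-Wallis is the only test named for change over time in alpha-diversity, which is one component of the trial's single secondary outcome. In a trial of 10 and 5 participants, using each person as their own control is a main source of information. A real change could be reported as no change because of the test. The Discussion expects the microbiota results to inform dosing and frequency in later work, so a misleading null result could carry forward.

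This is not a detail left for a statistical analysis plan. The article names a specific test, and it does not fit the data described.

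**Working it through.** **Inputs from the protocol article.** Three time points per recipient; arms of 10 and 5; a minimum of 10 completers out of 15. The article states no power, significance level, effect size, SD or within-person correlation for this test, so there is no figure of its own to reproduce.

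**Assumptions.** Nominal level 5%. Normal data with total SD 1. One correlation ρ between any two samples from the same person. Weeks 2 and 8 both shifted by the same amount from baseline.

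**Statistics**, with n people, k = 3 time points and N = 3n:

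- Kruskal-Wallis: H = 12/[N(N+1)] × Σ(R_j²/n) − 3(N+1), where R_j is the sum of the overall ranks at time j. H is compared with the chi-square value on 2 df, 5.99.
- Friedman: Q = 12/[nk(k+1)] × ΣR_j² − 3n(k+1), with ranks taken within each person. Q is compared with its simulated exact cut-off, 6.2 for n = 10.

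**Direction of the error.** Differences between time points vary only with the within-person part of the variance, 1 − ρ. H is scaled as if they varied with the whole variance. With ρ > 0, H is too small on average and p is too large.

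**Simulated size and power, n = 10, shift 0.8 SD.** Repeat runs of 40,000 or more data sets per cell move these figures by at most about one percentage point.

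| ρ | Kruskal-Wallis type I error | Kruskal-Wallis power | Friedman power |
|---|---|---|---|
| 0 | 4.6% | 37% | 28% |
| 0.3 | 1.7% | 33% | 38% |
| 0.5 | 0.6% | 30% | 51% |
| 0.7 | 0.1% | 26% | 74% |
| 0.9 | <0.01% | 25% | 99% |

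Friedman's own type I error stays at 4.4% to 4.7% for n = 10 at every correlation.

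**Share of Friedman's power lost at 0.8 SD**, from the table: (38 − 33)/38 = 13% at ρ = 0.3; (51 − 30)/51 = 41% at 0.5; (74 − 26)/74 = 65% at 0.7; (99 − 25)/99 = 75% at 0.9.

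**Other shifts, n = 10** (Kruskal-Wallis vs Friedman):

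- 0.5 SD: 16% vs 13% at ρ = 0; 11% vs 17% at 0.3; 8% vs 22% at 0.5; 5% vs 35% at 0.7; 3% vs 80% at 0.9. The loss from ρ = 0.3 upward is about 35%, 65%, 86% and 97%.
- 1.0 SD: 54% vs 42% at ρ = 0; 53% vs 56% at 0.3; 52% vs 71% at 0.5; 51% vs 90% at 0.7; 52% vs 100% at 0.9. The loss from ρ = 0.3 upward is about 6%, 27%, 43% and 48%.

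**Placebo arm, n = 5.** Kruskal-Wallis type I error is 2.0%, 1.0% and 0.3% at ρ = 0.3, 0.5 and 0.7. Power for 0.8 SD is 13% vs 17%, 11% vs 23% and 9% vs 35%.

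**Effect of attrition on the choice of replacement.** If loss is proportional (an assumption), the active arm falls to 10 × 10/15 ≈ 7 complete sets. At n = 7 Friedman's exact size is only 2.7%, because its distribution is coarse. For 0.8 SD at ρ = 0.5, power is 17% for Kruskal-Wallis, 28% for Friedman and 47% for repeated-measures analysis of variance. At ρ = 0.3 the figures are 20%, 20% and 35%. The normal data assumed here favour the last method.

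**The case against.** The strongest reply is that the article disclaims power for every microbiota outcome, so a loss of power contradicts nothing it promises. It adds that the error is conservative and so cannot create a false claim of change. Both statements are true and they lower the severity. They do not make the test valid: the disclaimer concerns sample size, while the article still plans these tests and corrects them for multiplicity.

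A second reply is that the within-person correlation is unknown. It may be low in the active arm, because the intervention is meant to move recipients towards the donor profile. This stands. A uniform shift with stable person effects suits Friedman well, and at correlation 0 Kruskal-Wallis does better. A reader might infer that most of the power is lost. The documents do not support that as a general statement, because they give neither correlation nor effect size. In the simulations with n = 10, the loss exceeds half from a correlation of about 0.5 for a 0.5 SD shift, or about 0.7 for 0.8 SD. For 1.0 SD it stays below half.

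A third reply is that the groups in the quoted sentence may be donors and recipients, so that recipients would be pooled across arms. The figures for 10 and 5 people would then not describe the planned test exactly, but the dependence between samples would be the same.

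A reader might also extend the criticism to the PERMANOVA over time. The article does not say how permutations are done, and that detail is commonly left to a fuller document, so no error is shown there.

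**Conclusion.** Wrong as written. The named test assumes independence that the sampling schedule rules out, under either reading of the groups. With positive within-person correlation its p-values are too large, and a null result over time cannot be taken at face value. The type I error figures rest on normal data with equal correlation between visits; the power figures also rest on the assumed shift. The loss ranges from none at correlation 0 to about three quarters at 0.9 for a 0.8 SD shift.

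This should be fixed, but it does not threaten the trial. Alpha-diversity is one component of the secondary outcome, beside beta-diversity, differential abundance, functional potential and engraftment. No target in Table 4 uses it, and the primary feasibility and safety outcomes are untouched. Nor would a better test make the small placebo arm informative: with 5 people at correlation 0.7, Friedman reaches only 35% for a 0.8 SD shift.

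**What to change.** Replace Kruskal-Wallis for the over-time comparison with a repeated-measures method. The preferred choice is a linear mixed model for each alpha-diversity index, with time as a fixed effect and a random participant effect, on a transformed scale if the index is skewed. It keeps participants who lack a week 8 sample. That matters because Table 4 requires only the baseline and week 2 stool samples, and Friedman would drop anyone without all three. Friedman can be used for complete triplets. The same sentence should say whether the groups are the two arms or all recipients.

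The cost is one sentence in the analysis section. No new data, samples or visits are needed.
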